### Statistical analysis

Continuous variables will be summarized as mean ± standard deviation (SD) if approximately normally distributed, and as median with interquartile range otherwise; categorical variables will be presented as counts and percentages. Baseline characteristics will be evaluated descriptively without formal hypothesis testing, in accordance with standard recommendations for randomized controlled trials, which discourage statistical testing of baseline variables. All analyses will be performed according to the intention-to-treat (ITT) principle.

For comparisons between groups, t-tests or Mann–Whitney U tests will be applied to continuous variables depending on the distribution assessed using the Kolmogorov–Smirnov test with Lilliefors correction. Categorical variables will be compared using chi-square tests or Fisher’s exact tests, as appropriate.

The primary endpoint of this RCT is the incidence proportion of IH at the mini-laparotomy site. Differences between groups will be evaluated using a two-sided chi-square test for proportions with a two-sided significance level of 5%, based on the prespecified hypothesis that CBS reduces the risk of IH compared with IS. The primary analysis population will include all randomized participants according to the ITT principle. A per-protocol set (PPS) analysis will be conducted as a sensitivity analysis including those who complete the allocated intervention according to the protocol.

Secondary endpoints—including intraoperative outcomes, early postoperative outcomes, the incidence of intraoperative complications, and readmission within 90 days after surgery—will be summarized descriptively for each group.

For the primary endpoint analysis, the incidence proportion of IH during the follow-up period and the corresponding 95% confidence intervals will be calculated for each group. In addition, the odds ratio and 95% confidence interval for IH incidence in the CBS group relative to the IS group will be estimated.

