## Current status of midline mini-laparotomy closure in Japan (based on our original survey)

In Japan, fascial closure of midline incisions has traditionally been performed using IS, which has long been regarded as the standard method for midline fascial closure. In our nationwide survey conducted in 2024 across 50 institutions, 3 institutions (6%) reported using continuous suturing, 45 institutions (90%) used IS, and 2 institutions (4%) reported using both techniques. The survey also revealed that, in cases where IS was applied, more than half of the institutions (58%) responded that the knot tying was performed by surgeons with less than three years of surgical experience. This suggests that the involvement of relatively inexperienced surgeons in knot tying may contribute to the occurrence of IH through loosening of knots in IS.

Although several retrospective studies from Japan have examined the incidence of IH after laparoscopic colorectal surgery, none have directly compared continuous and IS for fascial closure. Consequently, the evidence base remains limited [19, 21]. As a result, continuous suturing has not yet been widely adopted in Japan in the context of laparoscopic or robotic colorectal surgery.

At Nagoya City University, midline incisions in colorectal surgery are closed using continuous suturing with STRATAFIX Symmetric PDS Plus, a barbed suture. STRATAFIX Symmetric PDS Plus, manufactured by Ethicon (Johnson & Johnson, Raritan, NJ, USA), is a barbed suture that does not require knot tying. By incorporating anchoring points to prevent loosening and eliminating the need for continuous traction, it addresses the main drawback of conventional continuous suturing—loss of tension along the suture line—which can lead to the development of IH. In our institution, among 215 cases performed between June 2022 and December 2023, the incidence of IH at one year postoperatively was 3.5%.

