## Methods/design

### Trial design

The HIBISCUS trial is designed as a prospective, multicenter, open-label RCT comparing CBS with IS.

The HIBISCUS trial is a multicenter, prospective, open-label, randomized controlled study comparing continuous barbed suturing with interrupted monofilament suturing for fascial closure of mini-laparotomy incisions (Fig. 1). The study is conducted across six participating institutions in Aichi Prefecture, Japan. Eligible adults with colorectal cancer undergoing elective laparoscopic or robot-assisted resection will be randomized in a 1:1 ratio to continuous closure using a barbed absorbable suture (STRATAFIX Symmetric PDS Plus; bite width of 5 mm and stitch spacing of 5 mm) or interrupted closure using a monofilament absorbable suture (PDS Plus; bite width of 8 mm and stitch spacing of 8 mm). This study is registered in the Japan Registry of Clinical Trials (jRCT1040250129). Registration date: November 21, 2025. Ethical approval was obtained from the Certified Review Board of Nagoya City University, and the protocol has been reviewed and approved by the institutional review boards of all participating hospitals. Patients will be recruited from six hospitals in Aichi Prefecture. The planned enrollment period is 1.5 years, followed by a 1.5-year follow-up period, resulting in a total maximum follow-up duration of 3 years. The study protocol was developed in accordance with the Standard Protocol Items: Recommendations for Interventional Trials (SPIRIT) 2013 guidelines.

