### Randomization procedure

Randomization is performed within the same REDCap platform using a stratified block randomization method. Stratification factors include participating institution, body mass index (BMI; <25 kg/m² or ≥ 25 kg/m²), and sex (male or female), as BMI and sex are established risk factors for incisional hernia and may influence abdominal wall characteristics and wound healing. A fixed block size is used within each stratum to ensure balance between the treatment groups. Once patient eligibility is confirmed in REDCap, allocation to either the continuous barbed suturing (CBS) group or the interrupted suturing (IS) group is automatically generated by the system. This automated process ensures allocation concealment and minimizes the potential for investigator-related bias in treatment assignment.

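### The primary test is an unadjusted chi-square although randomisation is stratified by institution, BMI and sex: valid, but mildly conservative and slightly inefficient if those factors are prognostic

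*Protocol article*

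**What the plan says.** Design. The Randomization procedure section states: "Randomization is performed within the same REDCap platform using a stratified block randomization method". It continues: "Stratification factors include participating institution, body mass index" (cut at 25 kg/m²) and sex. The reason given for the two patient-level factors is that "BMI and sex are established risk factors for incisional hernia". Under Trial design, "The study is conducted across six participating institutions in Aichi Prefecture, Japan".

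Analysis. The Statistical analysis section fixes the primary comparison: "Differences between groups will be evaluated using a two-sided chi-square test for proportions with a two-sided significance level of 5" per cent. It adds the hernia proportion in each group with a 95% confidence interval, and says that "the odds ratio and 95% confidence interval for IH incidence in the CBS group relative to the IS group will be estimated". No stratification or covariate is attached to any of these. The only sensitivity analysis named for the primary endpoint is the per-protocol set.

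The Sample size calculation section uses the same test, a two-sided chi-square for proportions, with 11.5% against 3.9%, 80% power and 192 patients per group.

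**The concern.** Stratified blocks on prognostic factors force the two arms to be alike on those factors, which reduces the true variance of the difference between arms. An unadjusted chi-square computes its variance as if that balance had arisen by simple randomisation. Its standard error is then somewhat too large, its interval somewhat too wide and its actual level below 5%. The protocol takes the trouble to stratify, justifies two of the three factors by their effect on hernia, and then does not use them.

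This is a written choice of primary test, so it is not a detail left to an analysis plan that is not shown. A later plan with a stratified primary test would depart from the protocol.

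At stake is a little precision in a trial that expects about 30 hernias. Prespecification also matters: with so few events the unadjusted and stratified p-values could fall on opposite sides of 0.05, and choosing between them after unblinding would be post hoc.

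**Working it through.** **1. The plan's own figure.** Inputs from the Sample size calculation section: p₀ = 0.115, p₁ = 0.039, two-sided 5%, 80% power. The pooled proportion is (0.115 + 0.039)/2 = 0.077.

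n per group = [1.960·√(2·0.077·0.923) + 0.8416·√(0.115·0.885 + 0.039·0.961)]² / (0.115 − 0.039)²
= [0.7389 + 0.3141]² / 0.005776 = 1.1088 / 0.005776 = 191.97, so **192**.

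The stated 192 per group reproduces exactly. Sample size and primary test agree with each other.

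**2. How thin the strata are.**
- Strata: 6 institutions × 2 BMI classes × 2 sexes = 24.
- Patients per stratum: 422/24 = 17.6 on average.
- Expected events: 192 × 0.115 + 192 × 0.039 = 22.1 + 7.5 = 29.6 among 384 patients, or 29.6/24 ≈ 1.2 per stratum.

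**3. Unadjusted against stratified test, by simulation.** The document gives no effect size for BMI, sex or institution, no block size and no stratum proportions, so all of these are assumed. Main simulation: 40,000 runs, 384 patients, permuted blocks of 4, 30% with BMI ≥25, 57% male, and site shares of 30/20/15/15/10/10%. Overall rates were held at 11.5% and 3.9% for power, and at 11.5% in both arms for type I error. Scenarios are labelled odds ratio for BMI / odds ratio for sex / SD of institution effects on the log-odds scale. CMH is the Cochran-Mantel-Haenszel test.

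| Assumed strength | Type I error: chi-square / CMH 24 strata / CMH BMI × sex | Power: chi-square / CMH 24 strata / CMH BMI × sex |
|---|---|---|
| None (1 / 1 / 0) | 4.95 / 4.91 / 4.93% | 82.1 / 81.6 / 81.8% |
| Moderate (2 / 1.5 / 0.3) | 4.70 / 4.97 / 4.80% | 82.3 / 82.2 / 82.4% |
| Strong (3 / 2 / 0.5) | 4.26 / 4.85 / 4.59% | 82.7 / 83.3 / 83.1% |
| Very strong (4 / 3 / 0.8) | 3.86 / 5.14 / 4.52% | 83.2 / 85.0 / 84.3% |

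The Monte Carlo standard error of a single rate is √(0.05·0.95/40,000) = 0.11 points for type I error and √(0.82·0.18/40,000) = 0.19 points for power. Simulated power sits near 82% rather than 80% because the sample size formula is a normal approximation. Exact binomial enumeration with 192 per group and no stratum effects also gives 82.1%.

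**4. Other runs at similar strength (3 / 2 / 0.6), chi-square against 24-stratum CMH.**
- 12,000 runs: type I error 4.5% against 5.1%; power 81.6% against 82.4% (+0.8).
- 6,000 runs for power and 8,000 for type I error: 4.4% against 5.1%; 78.0% against 79.4% (+1.4).

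The absolute power levels differ between simulations, so only the within-simulation differences should be read.

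**5. Reading.** With strong factors, the chi-square runs at about 4.3–4.5% and gives up about 0.6–1.4 points of power. With moderate factors the power difference is within noise. With no prognostic effect, CMH on 24 strata loses 82.1 − 81.6 = 0.5 points.

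**6. Sparsity.** At the design rates, about 9 to 11 of the 24 strata (8.6 to 10.7 on average) have no event or only one arm, and so add nothing to the CMH test. With BMI × sex alone, part of the gain remains: under strong factors, +0.4 points of power and a type I error of 4.59%.

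**The case against.** The strongest reply is that the plan is coherent and its test is safe. The trial is sized on the test it will use, the figure reproduces, and the chi-square stays at or below its nominal level in every scenario of the main simulation. The benefit of stratifying is small, depends on strengths that the document does not give, and turns into a small loss if the factors are not prognostic. All of this stands, and it limits the weight of the point. It does not remove it, because the protocol itself asserts that BMI and sex are prognostic and the change costs almost nothing.

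Sparsity is also a fair objection to stratifying over all 24 cells. It is an argument for a prespecified fallback, not for ignoring the factors.

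A reader might infer more than the documents support:

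- *That the primary p-value is invalid.* It is not. The departure is towards conservatism, so it does not raise the risk of a false claim of superiority.
- *That the odds ratio is biased towards 1.* An unadjusted odds ratio lies nearer 1 than a conditional one because odds ratios are non-collapsible; it is a different, legitimate quantity. The gap is also small. The marginal value is (0.039/0.961)/(0.115/0.885) = 0.312, against about 0.30 and 0.29 conditionally with BMI/sex odds ratios and site SD of 2.5/1.5/0.5 and 3/2/0.6 (assuming 30% with BMI ≥25 and 55% male).
- *That site practice makes institution a strong prognostic factor.* The survey section says: "At Nagoya City University, midline incisions in colorectal surgery are closed using continuous suturing with STRATAFIX Symmetric PDS Plus". It also reports interrupted closure at 90% of 50 institutions nationwide. That survey does not describe the six trial sites, the protocol calls only BMI and sex risk factors, and the Implementation section requires competence in both techniques at every centre. Unequal familiarity with one technique would mainly produce a treatment-by-site interaction, which a common odds ratio does not address.

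**Conclusion.** The point holds as one of efficiency and good practice. The stated primary analysis does not use the stratification factors although the protocol calls two of them established risk factors, and no stratified or adjusted analysis is named alongside it. The test is valid and at most mildly conservative.

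The size rests on assumed strengths, stratum proportions and blocks of 4. Even under the most extreme scenario tried, the power difference is about 1.9 points before rounding (83.18% against 85.04%). Nothing here suggests that the sample size or the 5% level is wrong.

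**What to change.** Amend the Statistical analysis section before unblinding:

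1. Primary test: a two-sided Cochran-Mantel-Haenszel test at 5%, stratified by institution, BMI (<25 / ≥25 kg/m²) and sex.
2. Estimates: a Mantel-Haenszel common risk difference and common odds ratio, each with a 95% confidence interval from a variance formula suited to sparse strata. With about 30 events this is safer than a logistic model with a parameter for each of the 24 strata.
3. A sparsity rule fixed in advance, for example based on pooled event counts read without treatment codes, under which the strata collapse to BMI × sex.
4. Supporting analysis: the unadjusted chi-square with the group proportions and marginal odds ratio as now planned.

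Cost: a few sentences. No new data are needed, since all three factors must be known to allocate a patient, and the sample size stays at 422. The downside is a power loss of about 0.5 points if the factors turn out not to be prognostic.

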### Monitoring

Monitoring will be conducted to confirm the progress of the study and to ensure that it is implemented in accordance with the Ethical Guidelines and the approved study protocol. The principal investigator will appoint monitoring staff, who will be responsible for preparing and submitting monitoring reports to the study coordinating center. Monitoring staff will review source documents, including medical records and case report forms, approximately every six months from the date of the first patient registration. They will assess the following monitoring items and prepare a monitoring report.

The study representative will also prepare a central monitoring report approximately every six months from the start of enrollment, based on data aggregated from each participating institution.

### Central monitoring items

Registration status (number of enrolled cases across all institutions)Case information (baseline characteristics, study progress, details of discontinued cases)Case report form (CRF) entry status, including query managementDeviations from the study protocolOther issues affecting study progress

Following each site monitoring visit, the monitoring staff will promptly prepare and submit a site monitoring report.

#### Site monitoring items

Registration status (number of cases enrolled at the site)Eligibility assessment for each registered casePresence or absence of serious adverse eventsPresence or absence of major protocol deviationsOther site-specific issues related to study progress, safety, or data reliabilityCompliance with relevant ethical guidelines

## Discussion

This RCT aims to evaluate whether CBS is superior to IS in reducing the incidence of IH in patients undergoing laparoscopic or robot-assisted colorectal surgery. In recent years, advances in suture technology and the widespread adoption of minimally invasive and robotic colorectal surgery have renewed interest in optimizing fascial closure techniques for small midline incisions. However, despite emerging experimental and clinical data suggesting the safety and potential advantages of barbed sutures, high-quality randomized evidence in this specific surgical context remains limited.

Standardizing surgical technique is a major challenge in studies evaluating fascial closure methods, particularly in multicenter trials where surgeons with different levels of experience may contribute to variability. To minimize such variability, only surgeons who successfully completed a pre-trial competency assessment using a synthetic abdominal wall bench model were permitted to perform fascial closure, ensuring technical uniformity across all participating centers. Nevertheless, learning-curve effects and inter-center variability may still have influenced the results, and these factors should be considered when interpreting the findings.

The rationale for selecting an 8-mm bite width and 8-mm suture spacing for IS and a 5-mm bite width and 5-mm spacing for CBS is based on both existing evidence and prevailing clinical practice. For CBS, the 5-mm/5-mm parameters were chosen according to the STITCH trial, which demonstrated that a 5-mm bite width with 5-mm spacing significantly reduced the incidence of IH compared with a 10-mm bite width and 10-mm spacing protocol [30]. For IS, a nationwide survey of 50 institutions showed that 8-mm bites and 8-mm spacing were the most commonly used settings in Japan. After detailed discussion among all participating centers, these parameters were adopted to reflect real-world surgical practice and to enhance the pragmatic nature and generalizability of the trial.

In addition, the use of different suture calibers between the two groups warrants clarification. In this trial, a size 1 barbed suture was used for continuous closure, whereas a size 0 monofilament suture was used for interrupted closure. This decision was not intended to introduce differences in tensile strength or biomechanical performance between the two techniques. Rather, it reflects product-specific characteristics and prevailing clinical practice patterns. The same nationwide survey demonstrated that size 1 sutures are most commonly used for continuous fascial closure, whereas size 0 sutures are predominantly used for interrupted closure in Japan. After careful discussion among all participating centers, these suture calibers were selected to align with routine clinical usage and to preserve the external validity of the trial. Nonetheless, we acknowledge that the use of different suture sizes represents a potential limitation and should be taken into account when interpreting the results.

Standardizing bite width and suture spacing is essential in RCTs comparing IS and CBS because such standardization strengthens reproducibility and internal validity by minimizing inter-institutional and inter-surgeon variations. Moreover, this trial may serve as a standardized model for future international studies and contribute to global optimization of fascial closure strategies.

If CBS is shown to be superior to IS in reducing IH, CBS could become the preferred fascial closure method in minimally invasive colorectal surgery. Conversely, if CBS does not demonstrate superiority, IS would remain the standard approach, and the routine use of CBS may not be recommended. Regardless of the outcome, current evidence comparing CBS and IS remains limited and heterogeneous; therefore, this trial is expected to make an important contribution to evidence generation in this field and to inform future clinical guidelines and surgical practice.

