### Sample size calculation

Regarding the primary endpoint of IH, previous reports in laparoscopic surgery have shown an incidence of approximately 5–13% in patients undergoing conventional IS closure [17, 19–21]. Based on these data, an incidence of 11.5% was selected as a representative estimate for the IS group in the present trial.

In contrast, Pyo et al. reported an IH rate of 1.3% at 12 months following fascial closure with a monofilament polydioxanone barbed suture (MONOFIX^®^) in a prospective single-arm trial [22]. In our institution, the 1-year postoperative incidence of IH was 3.5% among 215 consecutive cases performed between June 2022 and December 2023.

Based on these previous findings, the incidence of IH in the CBS group was hypothesized to be reduced by approximately two-thirds compared with IS, resulting in an estimated incidence of 3.9%. With a two-sided significance level of 5% and a statistical power of 80%, the required sample size calculated using a two-sided chi-square test for proportions was 192 patients per group (total 384).

Allowing for an anticipated 10% dropout rate, the final target sample size was set at 422 patients. The calculation was performed using Stata software, version 17.0 (StataCorp, College Station, TX, USA).

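### The Discussion moves from no demonstrated superiority to not recommending barbed closure, though power for a halving of hernia risk is only 52–56%, and bite width and spacing are missing from the stated limitations

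*Protocol article*

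**What the plan says.** The Discussion of the protocol article gives an interpretation for each outcome. On a positive result: "If CBS is shown to be superior to IS in reducing IH, CBS could become the preferred fascial closure method". On a negative result: "Conversely, if CBS does not demonstrate superiority, IS would remain the standard approach, and the routine use of CBS may not be recommended".

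The section on sample size calculation fixes the effect for which the trial is powered. For control risk it reports that "previous reports in laparoscopic surgery have shown an incidence of approximately 5–13% in patients undergoing conventional IS closure", and then "an incidence of 11.5% was selected as a representative estimate for the IS group in the present trial". For the effect, "the incidence of IH in the CBS group was hypothesized to be reduced by approximately two-thirds compared with IS", which gives 3.9%. With a two-sided 5% level and 80% power, this leads to 192 per group, and to 422 in total after a 10% dropout allowance.

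The section on statistical analysis plans a two-sided chi-square test in all randomized participants, the incidence with 95% interval in each group, and an odds ratio with 95% interval. The article does not link the negative interpretation to any of these intervals or to a smallest worthwhile effect.

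Under Interventions, CBS uses a size 1 suture with 5 mm bites and 5 mm spacing, and IS a size 0 suture with 8 mm bites and 8 mm spacing. To justify 5/5 mm, the Discussion cites an earlier trial of small against large bites, "which demonstrated that a 5-mm bite width with 5-mm spacing significantly reduced the incidence of IH", the comparator there being 10/10 mm. It names the calibre difference as a potential limitation. It does not name bite and spacing as one; it credits their standardization with strengthening internal validity.

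**The concern.** Two separate problems affect what the trial can be said to show.

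First, failure to reject the null hypothesis is carried over into a statement about routine use. In a trial sized for a very large effect, a non-significant result can sit alongside a substantial true benefit. Retaining current practice after such a result is ordinary. Counselling against the alternative is a further step, which needs an interval that excludes a worthwhile benefit. The article expects its results to inform guidelines whatever the outcome, so the wording matters.

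Second, the contrast between the arms is a bundle: technique and suture, bite and spacing, and calibre. The article's own evidence treats bite and spacing as affecting hernia risk, in a direction that favours the CBS arm. Standardizing them within each arm reduces variation between surgeons and centres. It does nothing about the difference between arms, because each arm is standardized to different values. A reader could therefore take a positive result as an effect of continuous or barbed suturing as such, which the design cannot isolate.

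**Working it through.** **Inputs (sample size calculation, trial design and statistical analysis sections).** Control risk 11.5%; CBS risk 3.9%; two-sided α = 0.05; power 80%; 192 per group before dropout; 422 in total, so 422/2 = 211 per group; 1:1 allocation; uncorrected chi-square test. The halving is an assumption of this review, not a figure in the article: 11.5%/2 = 5.75%.

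**Formulas.** With p̄ = (p1+p2)/2, s0 = √[2p̄(1−p̄)] and s1 = √[p1(1−p1)+p2(1−p2)]:
- n per group = [(1.960·s0 + 0.8416·s1)/(p1−p2)]²
- power = Φ{[√n·(p1−p2) − 1.960·s0]/s1}

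**Step 1: the plan's own figure.** For 11.5% against 3.9%: p̄ = 0.077, s0 = 0.3770, s1 = 0.3732, difference 0.076. n = 191.97, rounded up to 192. Power at 192 is 80.0%. The stated figure reproduces.

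**Step 2: a halving.** For 11.5% against 5.75%: p̄ = 0.08625, s0 = 0.3970, s1 = 0.3949, difference 0.0575.
- n = 192: Φ(0.047) = 51.9% (exact binomial enumeration 52.6%).
- n = 211: Φ(0.145) = 55.7% (exact 56.0%).
- For 80% power, n = 373.01, so 374 per group.

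**Step 3: other effects at 192 per group and an 11.5% control rate.**

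| Relative reduction | CBS risk | Power |
|---|---|---|
| 66% (planned) | 3.9% | 80% |
| 60% | 4.6% | 70% |
| 50% | 5.75% | 52% |
| 40% | 6.9% | 34% |

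At the ends of the article's 5–13% control range, power for a halving with 192 per group is 25% (5% against 2.5%) and 57% (13% against 6.5%).

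**Step 4: an illustrative result, not a forecast.** IS 22/192 = 11.46%, CBS 12/192 = 6.25%, so CBS is 45% lower.
- Difference 5.21 points; pooled z = 1.80; p = 0.072.
- Standard error 2.89 points; 95% interval 5.21 ± 1.96 × 2.89 = −0.5 to +10.9 points.
- Odds ratio (12 × 170)/(22 × 180) = 0.52, 95% interval 0.25 to 1.07.

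The planned benefit is 11.5 − 3.9 = 7.6 points, an odds ratio of (0.039/0.961)/(0.115/0.885) = 0.31. Both intervals contain it. The result fails the test but does not rule out the effect for which the trial was sized.

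**Step 5: what differs between the arms.**

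| Component | CBS | IS | Named as limitation? |
|---|---|---|---|
| Technique and suture | continuous, barbed | interrupted, monofilament | it is the question |
| Bite / spacing | 5 / 5 mm | 8 / 8 mm | no |
| Calibre | size 1 | size 0 | yes |

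**The case against.** The quoted sentences are hedged Discussion prose (could, may not), not a prespecified criterion. A reader might infer a decision rule under which p ≥ 0.05 triggers a recommendation, but nothing in the sample size or analysis sections sets one. IS is used at 90% of the surveyed institutions, so keeping it when superiority is not shown is the usual default. The article nowhere says that CBS would then be shown not to work, and the interval needed to judge the matter is already planned. Every trial also loses power below its design effect, and the halving is not the article's own target.

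On attribution, a reader might infer that the article would credit continuous or barbed suturing alone. It does not. The arms are defined with their suture, bite and spacing, calibre is flagged for interpretation, and the 5/5 against 8/8 mm difference is disclosed and defended as pragmatic. A comparison of two packages is a legitimate design. The cited trial compared 5/5 with 10/10 mm, not with 8/8 mm.

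All of this stands, and it limits the point to interpretation. It leaves two gaps. The negative sentence goes beyond keeping the default and is not tied to the planned interval. And the one limitation stated about differences between the arms omits the component for which the article itself cites evidence of an effect on hernia.

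**Conclusion.** The point holds as one about interpretation and calls for a change of wording. At an 11.5% control rate, a true halving of hernia risk would miss significance about 44% of the time (211 evaluable per arm) to 48% (192 per arm), and more often if control risk is lower. Non-significance alone is therefore not evidence against CBS. These figures rest on the uncorrected chi-square test, the 11.5% control rate and the choice of a halving as the alternative.

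It does not follow that an inconclusive result is likely. Under the article's own assumptions power is 80%, and the shortfall arises only if the true effect is smaller than planned or the control risk is lower.

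On attribution, a positive result would support the CBS package over the IS package. It would not isolate continuity or barbs. A reader might want to say how much of the planned 7.6 points bite and spacing could explain. The article gives no effect size for them, and none for 5/5 against 8/8 mm, so no share can be stated.

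**What to change.** Change the wording before results are known.

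(a) In the Discussion, keep the statement that IS remains the default if superiority is not shown. Replace the statement on routine use of CBS with an interpretation based on the 95% confidence interval of the between-arm effect: the planned odds ratio, ideally with a risk difference. State the smallest worthwhile reduction in advance, and call a non-significant result inconclusive unless the interval excludes that reduction.

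(b) Add bite width and spacing to the limitation that now names only suture calibre. Make clear that standardization reduces variation within each arm and leaves the difference between arms in place. Word the objective and conclusions as a comparison of two closure packages (technique, suture, bite and spacing, calibre), with no claim about the continuous or barbed component alone.

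The cost is a somewhat narrower claim, plus the work of agreeing and recording a smallest worthwhile reduction. Interventions, sample size and procedures do not change.
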